**Ethics Board Timeline:**      **11.02.2015 Submission Deadline**

**10.03.2015 Meeting**

## **ABSTRACT**

### **Background:**

More than two thirds of sudden cardiac arrests are witnessed by bystanders. Bystander cardiopulmonary resuscitation (CPR) doubles survival from cardiac arrest. Importantly, even in witnessed cardiac arrests only 20% of the bystanders commence basic life support. Common reasons for not commencing include panicking and the perceived inability to perform CPR correctly. A meta-analysis could demonstrate that a simplification of the algorithm (compression-only dispatcher-assisted bystander CPR) led to a 22% increase in survival-to-hospital discharge. A recently published trial of the research group could demonstrate that the presence of a flowchart has a positive effect on the quality of BLS while at the same time increasing the rescuers' confidence. Nonetheless, performing CPR is exhausting. Previous publications have emphasized increasing fatigue with the duration of CPR efforts in both, standard and chest compressions-only CPR. Consequently, we wanted to test the hypothesis that chest compressions (CC) are delivered more correctly regarding the depth when utilizing the standard BLS algorithm with the aid of a flowchart as compared to the CC only algorithm utilizing an adapted CPR flowchart in a manikin resuscitation model.

### **Methods:**

After consent of the Research Ethics Board of Medical University of Vienna and obtaining written informed consent of the participants, 84 medically untrained laypersons will be randomised to perform flow-chart assisted CPR for 300s following standard CPR guidelines or CC only CPR. The primary outcome parameter will be the total number of CC achieving the correct depth of 50-60mm. Secondary outcome parameters will be hands-off time, the total number of CC, and the compression rate. The total number of delivered rescue breaths, tidal volume, and time to deliver these will also be evaluated. Furthermore, the subjective point of exhaustion affecting the CPR quality, the reason for discontinuation of CPR if stopped within the 300sec. period and the exhaustion at the end of the CPR measures will be evaluated.

## **Background:**

Since the introduction of the modern Basic Life Support (BLS) in the 1950, on-going efforts have been made to improve the quality of first aid measures [**Handley et al.** 2005, **Koster et al.** 2010]. International BLS algorithms have been designed, validated and published to meliorate the outcome after a cardiac arrest [**Koster et al.** 2010].

In many European countries cardiac arrest and sudden death due to coronary ischaemia is the primary single cause of death in adults. Across Europe, with a total population of approx. 830 Million inhabitants, emergency medical service treated cardiac arrest occurs in a range of 17-53/1000,000/year [**Gräsner et al.** 2013].

Many of these victims of sudden cardiac arrest could survive if bystanders would act immediately while shockable heart rhythms are still present, but successful resuscitation is unlikely once the rhythm has deteriorated to asystole [**Valenzuela et al.** 1998].

Chances of survival from witnessed ventricular fibrillation decreases by 7-10% every minute without cardiopulmonary resuscitation (CPR) [**Valenzuela et al.** 1998]. In urban areas, the Emergency Medical Services response interval is eight minutes or more [**vanAlemAP et al.** 2003]. Overall, bystander CPR doubles or triples survival from witnessed cardiac arrest [**Wissenberg et al.** 2013].

In most cases the fundament of a functional chain of survival is lay people who may or may not have been trained in BLS courses. Especially as more than two thirds of the sudden cardiac arrests are witnessed by bystanders [**Müller et al.** 2006]. Unfortunately, the frequency of initiating CPR by lay people is still seen to be very low. Reasons for this fact are among others, fear of making mistakes and thus harming the collapsed or reluctance to perform mouth-to-mouth ventilation [**Swor et al.** 2006, **Svastano et al.** 2011].

Evidence shows that skill acquisition and retention is, besides regular application of the algorithm, added by the simplification of BLS sequence [**Koster et al.** 2010]. In the process of improving the resuscitation guidelines it was one of the aims of the European Resuscitation Council to simplify the BLS algorithm and design a sequence that would be easy to remember and apply. A recently published trial of the research group could demonstrate that the presence of a flowchart has an additional positive effect on the quality of BLS [**[name] et al.** 2013].

A meta-analysis of three previously conducted trials could demonstrate that a simplification of the algorithm (compression-only dispatcher-assisted bystander CPR) led to a 22% increase in survival-to-hospital discharge [Hüpfel *et al.* 2010]. These findings were so convincing that they found representation in a scientific statement of the AHA regarding pre-arrival instruction by the dispatcher [Lerner *et al.* 2012].

Nonetheless, even when bystanders commence CPR, publications have demonstrated fatigue in both, standard and chest compressions-only CPR [Heidenreich *et al.* 2012, McDonald *et al.* 2013]. Despite the fact that chest compressions-only CPR lead to an increase in total number of delivered chest compressions (CC), the fraction of effective CC (reaching the recommended depth) declines among elderlies with the longer duration of CPR [Heidenreich *et al.* 2012]. Noteworthy, in a publication by McDonald and colleagues, fatigue did not affect the rate of compressions. Nevertheless, the compression depth was affected from the second minute onwards [McDonald *et al.* 2013]

This fact is of clinical relevance since for every 5mm increase in compression depth in out of hospital cardiac arrests, the odds of survival and survival with a functional outcome increase [Vadeboncoeur *et al.* 2014]. Even though the optimal depth remains disputed, the current ERC Guidelines recommend a depth of 50-60mm [Koster *et al.* 2010]. Furthermore, and a depth of >50mm has been shown to be associated with improved outcome as well as functional neurological outcome [Vadeboncoeur *et al.* 2014]. Nevertheless, the optimal depth is not undisputed since contrary to previously published data, a recent publication by Stiell and colleagues identified the peak in survival at 45.6mm, below the currently recommended depth [Stiell *et al.* 2014].

The guidelines also recommend a CC rate of 100-120/min [Koster *et al.* 2010]. This is in line with recently published data indicating that the maximum rate of survival to hospital discharge can be achieved when compressing at 100-120/min [Idris *et al.* 2015]. An increase in CC rate over 120/min can decline the probability of return of spontaneous circulation possibly due to a concordant reduction in compression depth [Monsieurs *et al.* 2012, Stiell *et al.* 2012].

Consequently, we wanted to test the hypothesis that chest compressions are delivered more correctly regarding the depth when utilizing the standard BLS algorithm with the aid of a flowchart as compared to the CC only algorithm utilizing an adapted BLS flowchart in a manikin resuscitation model.

## **Study Design**

The investigation will be conducted as a prospective, randomized controlled study performed by the Department of Anaesthesia, General Intensive Care and Pain Management, Medical University of Vienna, Austria, according to the Good Scientific Practise guidelines of the Medical University of Vienna. The data collection will be conducted in cooperation with the Training Centre of St. John Ambulance, Vienna, Austria.

## **Study Population**

Eligible are all volunteers of  $\geq 18$  years of age of non-medical profession, irrespective of gender. Exclusion criteria are professional medical training (nurses, medical doctors, physiotherapists, ergotherapists, emergency medical technician or equivalent), pregnancy (as by verbal response at the time of recruitment), and parallel participation in a clinical trial, or physical impairment or illness prohibiting physical effort.

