## Description of study days

Volunteers will be invited to participate in the trial by the study personnel. Recruitment will be conducted at a Training Centre of St. John ambulance, Vienna, Austria, before the starts of the lessons. After giving written informed consent, participants will be randomized using a web based randomization program

([www.random.org](http://www.random.org)) and allocated to perform standard CPR or CC only. The randomization for group allocation will be kept in opaque and sealed envelopes.

The evaluation will be performed with an independent investigator using a computer attached Resusci-Anne Skillreporter by Laerdal-Medical® and the Laerdal Skillreporter Software with Segstat (Version 2.3.0, Laerdal Medical, Stavanger, Norway).

The participants will be asked to perform BLS for five minutes on a manikin. The participants will then be asked to undertake any action they deem necessary to rescue the person simulated by the resuscitation manikin. Participants will not be informed about the underlying hypothesis or the outcome parameters. The room will be prepared to minimise outside interruptions.

Additionally, participants will be instructed to indicate the point in time during CPR when they feel that their fatigue is affecting the quality of the life support performed. ("During CPR and without stopping your actions, please tell us "NOW" when you perceive your fatigue is affecting the quality of the life support performed.)

Participants in both groups will receive one of the charts right at the beginning of the scenario with the information that "this chart will provide information on how to perform CPR" and with the start of the clock further instructions regarding its content. Both groups will not receive any further introduction or support. At the beginning of the scenario, the manikin will be positioned in a supine position on the floor. There will be no clock visible for the participant while performing CPR. An investigator is acting as bystander able to call the emergency medical service or to be sent to look for an automated external defibrillator (which will not be available in the scenario). Nonetheless, the investigator is instructed not to provide any information on how to perform CPR and does not physically take part in the primary check, CC, or mouth-to-mouth ventilations.

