Data of steps performed or left out will be documented in hardcopy on the case report form by an investigator and the exact times and details of chest compressions and ventilations will be documented electronically (Laerdal Skillreporter Software with Segstat (Version 2.3.0, Laerdal Medical, Stavanger, Norway)). Checklists of necessary steps will be created based on the ERC BLS Guidelines 2010 in the same manner as published previously [Roessler *et al.* 2007, Koster *et al.* 2010].

After the five-minute period has ended, the participants will be informed that the emergency medical service is now taking over and that they can stop performing CPR. Directly thereafter, they will be asked the following questions "How exhausted are you now on a scale from 1 to 10, where 1 indicates no exhaustion at all and 10

maximum exhaustion?" (Lickert Like 1-10). If a participant choses to abort resuscitation attempts before the five minutes are over, the open-ended question "Why did you discontinue the resuscitation attempts?" will be raised.

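### The abstract calls the participants medically untrained, but laypersons with earlier BLS or first-aid courses are eligible, and the protocol names prior training neither as an item to record nor as a randomisation factor

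*Protocol*

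**What the plan says.** The Methods paragraph of the abstract gives the population as follows: "84 medically untrained laypersons will be randomised to perform flow-chart assisted CPR for 300s following standard CPR guidelines or CC only CPR".

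The Study Population section sets eligibility by occupation. Volunteers must be adults, "years of age of non-medical profession, irrespective of gender", and the only criterion that concerns training is this: "Exclusion criteria are professional medical training (nurses, medical doctors, physiotherapists, ergotherapists, emergency medical technician or equivalent". Earlier lay courses are not mentioned.

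The Background describes the bystanders on whom survival usually depends as "lay people who may or may not have been trained in BLS courses".

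Description of study days gives the setting: "Recruitment will be conducted at a Training Centre of St. John ambulance, Vienna, Austria, before the starts of the lessons". Participants are then "allocated to perform standard CPR or CC only", using a web-based randomisation program and sealed envelopes. No stratification factor is named. Of the case report form, that section says: "Data of steps performed or left out will be documented in hardcopy on the case report form by an investigator". Nothing in the protocol names previous BLS or first-aid training as something to ask about.

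The hypothesis concerns compressions delivered when "utilizing the standard BLS algorithm with the aid of a flowchart as compared to the CC only algorithm utilizing an adapted BLS flowchart". It does not mention training status.

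**The concern.** The abstract's label and the eligibility rule need not describe the same people. Someone who has taken one or more first-aid courses but works outside health care meets the eligibility rule. Such people may well be found at a training centre.

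Three things are at stake.

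- **Applicability.** A conclusion worded for untrained rescuers would rest on a sample with an unknown share of trained ones.
- **Chance imbalance.** Earlier practice plausibly affects compression quality, and a trial of 84 without stratification can leave the arms noticeably unequal on it.
- **Effect modification or dilution.** Both interventions are charts given with little other support. A person taught compressions with ventilations might depart from the compression-only chart. If so, the difference between charts would vary with training, and nobody could see it unless training had been recorded.

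An analysis plan cannot repair this later, because an item not collected before randomisation can be neither stratified on nor reliably reconstructed.

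**Working it through.** **Inputs from the protocol.** 84 are recruited and 74 are needed for analysis (Sample Size). The allocation ratio is not stated; 1:1 is assumed, giving 42 or 37 per arm. Mean depth is 43 mm with SD 12 mm, and the target difference is 20%, read here as relative: 0.20 × 43 = 8.6 mm. Tests are two-sided at 0.05.

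**Inputs assumed.** The documents give neither the share p of previously trained participants nor the effect of training. I use p = 0.3 to 0.7 for imbalance, a trained share of 25-50% for power, and a depth shift of 5-10 mm where one is needed.

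**1. Chance imbalance.** Without stratification, the approximate limit exceeded in 5% of trials is 1.96 × √(2p(1−p)/n).

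| p | n per arm | Limit |
|---|---|---|
| 0.5 | 42 | 1.96 × √(0.50/42) = 0.214 |
| 0.3 or 0.7 | 42 | 1.96 × √(0.42/42) = 0.196 |
| 0.5 | 37 | 1.96 × √(0.50/37) = 0.228 |
| 0.3 or 0.7 | 37 | 1.96 × √(0.42/37) = 0.209 |

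This is about 20-21 percentage points at 42 per arm and 21-23 at 37. If training shifted mean depth by 5-10 mm, an imbalance of that size at 42 per arm would move the arm difference by 0.196 × 5 = 1.0 mm to 0.214 × 10 = 2.1 mm, against the planned 8.6 mm.

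**2. Training shifts depth equally in both arms.** The SD becomes √(144 + p(1−p)g²), where g is the shift.

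- Trained share 0.25, g = 5: SD = √148.7 = 12.2 mm.
- Trained share 0.5, g = 10: SD = √169 = 13.0 mm.

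Power for 8.6 mm at 37 per arm, which is 0.87 by the normal approximation with SD 12, then lies between 0.86 and 0.81. This loss is small.

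**3. Training changes the chart effect.** If the effect differs by D between trained and untrained people, the pooled estimate differs from the untrained effect by p × D, that is 0.3D to 0.7D, whatever the sample size. D is unknown.

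As an extreme illustration, suppose a share q does what it learned before and shows no arm difference. The difference becomes 8.6(1−q), with standard error 12 × √(2/37) = 2.79.

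- q = 0: 8.6/2.79 = 3.08, power 0.87.
- q = 0.25: 6.45/2.79 = 2.31, power 0.64.
- q = 0.50: 4.3/2.79 = 1.54, power 0.34.

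**4. What a stratum can show.** With p = 0.3, the smaller stratum has 0.3 × 84 ≈ 25 people, or 12-13 per arm. For 12 per arm the standard error is 12 × √(2/12) = 4.90. Then 8.6/4.90 = 1.76, and power is Φ(1.76 − 1.96) ≈ 0.42. For 13 per arm it is about 0.45.

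The millimetre and power figures in steps 1 to 4 are on the scale of mean depth, because that is the only outcome for which the protocol gives a mean and SD. They do not carry over directly to the primary outcome, the number of compressions at correct depth.

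**The case against.** The other side has a good deal right.

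- **The label can be read loosely.** Medically untrained may simply mean without professional medical training, which is exactly what the Study Population section applies. The Background also accepts that real bystanders are a mix of trained and untrained, so enrolling both fits the rationale. This stands: it is an ambiguity to be settled, not a proven contradiction.
- **The arm contrast is intact.** A reader might infer that the comparison is no longer the one stated. It does not follow. Training precedes randomisation and is balanced in expectation, and the assigned contrast is unchanged. Chance imbalance is also already allowed for in the test's type I error; adjustment improves precision and credibility rather than removing a bias.
- **No direction of bias is shown.** A reader might infer that carry-over favours the arm whose chart matches earlier teaching. Nothing in the documents demonstrates this or gives it a size.
- **Testing after teaching is not supported.** A reader might infer that someone recruited before a lesson could be tested after it. Description of study days runs from consent to randomisation to the test with no lesson between, and the Risk/benefit assessment places CPR information after data collection.
- **Silence is not proof.** The protocol lists no baseline variables, and the case report form is not shown. Prior training may be on it. All that can be said is that the protocol does not name it.

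The argument that this belongs in an analysis plan does not stand. Eligibility wording, pre-randomisation questions and randomisation strata are fixed by the protocol.

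**Conclusion.** The point holds in limited form. Laypersons with previous BLS or first-aid training are eligible for a trial whose abstract calls its participants medically untrained, and the protocol provides neither for recording that training nor for stratifying on it. The result would be valid for the mixed lay population enrolled. Whether it applies to untrained rescuers could not be judged.

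Chance imbalance would exceed about 20-21 percentage points in 5% of trials with 42 per arm, assuming 1:1 allocation and 30-70% previously trained. An equal effect of training in both arms would cost little power. A different effect by arm could cost much more, but its existence and size cannot be determined from the documents, so the 0.64 and 0.34 are illustrations and not predictions. The documents do not support saying that the contrast is altered, that the estimate leans towards one arm, or that anyone is tested after teaching. The change is still worth making because it is cheap and can only be made before enrolment.

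**What to change.** 1. In Description of study days, add one question to be asked before the envelope is opened: any previous BLS or first-aid course (no, or yes with year).
2. Prepare two envelope sets, one for previously trained and one for never trained participants. Each should come from a list balanced in blocks, because unrestricted randomisation within strata would not limit imbalance.
3. In Data management and calculations, adjust the primary comparison for this stratum, for example with a linear model containing arm and stratum. Give the arm difference within each stratum as descriptive only.
4. In the abstract, describe the participants as laypersons without professional medical training, so that it agrees with the Study Population section.

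The cost is one question, a second stack of envelopes, one degree of freedom in the primary model and a wording change. No participants or visits are added. The drawback is that stratum estimates will be imprecise, with power of roughly 0.4 in a stratum of 12-13 per arm, so they should not be used to claim an effect, or its absence, in either group.

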## **Withdrawal and replacement of subjects**

Subjects must be withdrawn under the following circumstances:

- at their own request
- if the subject violates the conditions laid out in the consent form/information sheet or disregards instructions by the study personnel

In all cases, the reasons why subjects are withdrawn must be recorded in detail in the case report form. Should the study be discontinued prematurely, all study materials (completed, partially completed and empty case report forms) will be retained.

Subjects who do not complete the study according to protocol will be replaced. The data from the replaced subjects will be eligible for analysis of the conducted trial periods and for safety variables.

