## Statistical Methods

### Outcome parameters:

The primary outcome is total number of CC achieving the correct depth of 50-60mm in five minutes of manikin CPR. With this the authors want to test the hypothesis that chest compressions are delivered more correctly regarding the depth when utilizing the standard BLS algorithm with the aid of a flowchart as compared to the CC only algorithm utilizing an adapted BLS flowchart in a manikin resuscitation model. The secondary outcome parameter is hands-off time (HOT), which is defined as the sum of total time elapsed during the 300sec. of BLS in which no chest compressions are provided. This includes the pre-compression interval where the initial steps of BLS are performed as well as all interruptions of the CC, e.g. in order to ventilate or pause due to any other reason including exhaustion. Furthermore, the total number of CC, and the compression rate will be evaluated. The total number of delivered rescue breaths, tidal volume, and time to deliver these will also be evaluated.

Furthermore, questions regarding following points will be raised: “During CPR and without stopping your actions, please tell us “NOW” when you perceive your fatigue is affecting the quality of the life support performed”, “How exhausted are you now (question raised directly after discontinuing the CPR) [McDonald *et al.* 2013] (Lickert Like Scale 1-10). If a participant choses to abort resuscitation attempts the open ended question “Why did you discontinue the resuscitation attempts?” will be raised.

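### The replacement rule does not say how early stoppers are treated, although stopping and exhaustion are study outcomes, so the arms could be selected on an outcome

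*Protocol*

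**What the plan says.** The protocol section Withdrawal and replacement of subjects gives two grounds for mandatory withdrawal. A participant is withdrawn "at their own request", or if he or she "violates the conditions laid out in the consent form/information sheet or disregards instructions by the study personnel". The section then adds a broader rule: "Subjects who do not complete the study according to protocol will be replaced". It does not define completion. The next sentence reads: "The data from the replaced subjects will be eligible for analysis of the conducted trial periods and for safety variables".

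Other sections treat stopping and exhaustion as results:

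- Abstract, Methods lists among the evaluated items "the reason for discontinuation of CPR if stopped within the 300sec. period".
- Statistical Methods, Outcome parameters defines the primary outcome as the number of compressions of correct depth in five minutes. It defines hands-off time as all time without compressions during the 300 s, including a "pause due to any other reason including exhaustion".
- Description of study days plans for the event: "If a participant choses to abort resuscitation attempts before the five minutes are over", an open-ended question about the reason is asked. Nothing there calls such a person withdrawn or replaced.

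Methodology, Sample Size raises the required 74 participants to 84 for an expected drop-out of about 10%.

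**The concern.** The task is five minutes of basic life support. Someone who gives up earlier has, in ordinary language, not completed it, and stopping by choice can also be read as leaving at one's own request. The withdrawal section can therefore be applied to exactly the participants whose stopping the outcome sections set out to measure. The protocol does not say which reading prevails.

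This matters because rescuer fatigue is the trial's rationale. If people who tire and stop are replaced by people who can finish, and the stoppers are then left out, the mean count of the arm with more stopping is raised after randomisation. The comparison becomes one between people able to finish, and part of any effect of the algorithm on fatigue is lost. Analysing stoppers only for the part they performed also conflicts with outcomes defined over the full five minutes.

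**Working it through.** **1. The texts side by side**

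| Question | Withdrawal section | Outcome and procedure sections |
|---|---|---|
| Is an early stop a valid observation? | Not stated; can be read as non-completion or as withdrawal at own request | Treated as an event to record, with its reason |
| Is the person replaced? | Yes, if this counts as not completing according to protocol | Not mentioned |
| Over what time is the person analysed? | The periods conducted, undefined for a single session | The full 300 s |

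The two columns cannot both be followed without a further decision.

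**2. The plan's own allowance for loss**

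Inputs from Sample Size: 74 needed, about 10% drop-out, 84 recruited. The 74 is taken as given here.

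74 / (1 − 0.10) = 82.2, so 83, or 84 as an even total for two arms. The figure of 84 reproduces. As recruited, it tolerates (84 − 74) / 84 = 11.9% loss without any replacement.

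**3. Illustration for one arm**

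The protocol gives no stopping rate, so all inputs here are assumptions. A share *a* of one arm stops halfway with half the full count, and the others have mean *M*.

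- Mean of everyone who started: *M* × (1 − 0.5*a*)
- Mean if stoppers are replaced and left out: *M*
- Overstatement: 1 / (1 − 0.5*a*) − 1

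| *a* | Calculation | Overstatement |
|---|---|---|
| 5% | 1 / 0.975 − 1 | 2.6% |
| 10% | 1 / 0.95 − 1 | 5.3% |
| 20% | 1 / 0.90 − 1 | 11.1% |
| 30% | 1 / 0.85 − 1 | 17.6% |

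**4. Illustration for the difference between arms**

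The assumptions, again not from the protocol, are 42 per arm, a full-session count of 200 (SD 80) in both arms, stoppers keeping 20% to 80% of their count, and stopping unrelated to ability. Mean differences (standard minus compression-only) over simulated trials:

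| Stopping, standard vs compression-only | Stoppers analysed | Stoppers replaced and left out |
|---|---|---|
| 0% vs 10% | 10.3 | 0.3 |
| 5% vs 15% | 10.5 | 0.4 |
| 5% vs 25% | 19.9 | 0.1 |
| 10% vs 10% | −0.2 | −0.2 |

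Hand check of the second row: stoppers lose half their count on average, so the expected difference is 200 × 0.5 × (0.15 − 0.05) = 10. The difference disappears when stoppers are left out and is preserved when they are analysed. With equal stopping there is nothing to lose. Which arm would have more stopping is also an assumption.

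**5. Partial analysis**

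If a stopper's raw count up to the stop is kept, it equals the 300 s count with zeros afterwards, so the primary outcome is unharmed. If the count is scaled to the time performed, half the count in half the time becomes a full count, and the overstatement in step 3 returns. Hands-off time is affected in either case: for a stop halfway, 300 − 150 = 150 s without compressions would not be counted.

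**The case against.** The strongest reply is that the protocol never calls an early stop a failure to complete. Exhaustion is not among the listed withdrawal grounds, and the procedure foresees aborting and attaches a question to it, so a stopper can fairly be read as a completed observation. The sentence after the replacement rule also keeps replaced participants' data available. These points stand, and they rule out the stronger reading that a reader might infer, namely that the analysed arms are selected on the outcome by rule. They do not remove the ambiguity. Being eligible for analysis is permissive, and a single continuous session has no defined periods.

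It can also be said that analysis sets belong in a statistical analysis plan. That is generally true, but replacement is carried out during recruitment under the protocol, and the conflict is between sections of the protocol itself.

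Three further inferences are not supported:

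- *Stopping will differ by arm.* The Background describes fatigue with both techniques and a fall in effective compressions over time. It predicts no difference in stopping rates.
- *People who depart from the chart are withdrawn.* The ground is that someone "disregards instructions by the study personnel". Participants are told to take any action they think necessary, and steps left out are recorded as data. Some doubt remains, because instructions on the chart's content are given when the clock starts.
- *The bias is a large part of the 20% design difference.* That 20% is stated for compression depth, whereas the illustration concerns counts. The two cannot be compared.

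Providing for loss both by recruiting 84 and by replacement is redundant, but it does not bias anything.

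**Conclusion.** The concern holds as an unresolved conflict that creates a risk of bias. The withdrawal section can be applied so that a participant who aborts from exhaustion is replaced and left out or only partly analysed, while other sections treat that event as an outcome within a fixed 300 s window. Selection on an outcome would follow only if two conditions hold together: stoppers are not fully analysed, and stopping differs between arms. If either fails, there is little bias in the comparison.

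The size cannot be determined from the protocol. The range of about 3% to 18% in one arm's mean is an illustration that assumes 5% to 30% stopping, half the full count at the stop, and full exclusion of stoppers.

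**What to change.** Reconcile the withdrawal section with Abstract (Methods), Outcome parameters and Description of study days before recruitment starts, by stating that:

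- anyone randomised who starts the scenario is not replaced for stopping early or for departing from the chart;
- that person is analysed in the assigned arm over the fixed 300 s, with zero further compressions after a stop and the remaining time counted as hands-off time;
- exclusion is limited to withdrawal of consent or technical failure of the recording, which the allowance of roughly 10% within the 84 already covers.

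This follows the protocol's own definitions of the primary count and hands-off time. It costs a few sentences and no additional participants. The small downside is that some low values stay in the data and add variance.
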